| --- |

| 1. **Research Design and Methods:**   **I. Study design:**  Single-blinded Randomized Controlled Trial and conducting a therapeutic protocol through Delphi method  **II. Subjects:**   - **Study Population:**   Hospitalized patients with severe COVID-19 pneumonia at Imam Khomeini Hospital Complex   - **Inclusion/exclusion criteria**   **Inclusion Criteria:**   1. Patients with COVID-19 pneumonia confirmed by RT-PCR test and diagnostic radiology. 2. 18 to 75 years old 3. Non-intubated patients 4. Patients with full consciousness 5. Be able to walk and perform exercises. 6. O2 Saturation < 88% when free air breathing. 7. be able to write and read in Farsi   **Exclusion Criteria:**   1. Any type of musculoskeletal disorder disabling patient to participate in the study. 2. Intubation during the period of intervention 3. Patients' dissatisfaction to continue the study for any reason. 4. Unable to complete at least three sessions of physiotherapy.   **III. Sample Size:**  Target variable: SPO_2_  Clinical significancy of SPO_2_: 4%  Standard Deviation: 8.8%  Type I error: .01  Power: 80%  Sample size: 13 per group  Final sample size after considering possible attrition: 20 per group  **IV. Methods:**  After receiving permission from ethical committee of Tehran University of Medical Sciences, patients admitted to pre-intensive care units and intensive care units with definite COVID-19 diagnosis who have severe clinical symptoms and aren’t intubated will be invited to participate in this study. After receiving informed consent, evaluation will begin. In this procedure, all outcome measurements including mixed venous blood gases, SpO_2_ in free air room and breathing through partial rebreather, distance of 3-minute-walk test and its perceived exertion and patients’ breathlessness will be measured. Before applying intervention, the investigator will conduct randomization through closed envelopes given to him/her. In this study, randomization will be done using Block balanced randomization method. This randomization method is the best way to homogenize study groups (34). The investigator who is responsible for applying intervention will allocate participants to the groups based on allocation concealment principles (35).  The duration of this study will be 3 days. This time was selected based on the mean of patients’ duration of stay in pre-intensive care units. This is an add-on randomized control trial study. Patients in both groups will receive consultation by physiotherapist with emphasis on breathing control and general exercises during hospitalization benefits of coughing and instruction on using incentive spirometer.  **Experimental group intervention:**  In this phase, patients receive respiratory physiotherapy two times a day (totally 6 sessions). This procedure includes patient evaluation, clinical decision making and applying interventions (27).   1. Evaluation:  - Vital signs (HR, RR, BP) - ECG - Drug chart - Body temperature - VBG or ABG - Pulmonary sounds (?) - Pulmonary palpation - SpO_2_ - Clinical imaging (CT-Scan or X-ray)  1. Clinical decision making:   Considering therapist’s clinical examination and findings in each session, 2 treatment protocols will be considered for the patient:  Patients with Excessive Pulmonary Secretions  At first, based on therapist’s diagnosis and clinical decision making, ACTs will be administered for the patient. This treatment continues as long as airway secretions signs will be improved significantly. After applying these techniques, the patient will be treated with indicated dose of breathing control and diaphragmatic breathing in patients without airway secretion.  These techniques will include active cycle of breathing technique (ACBT), Autogenic Drainage, percussion, vibration, postural drainage and effective cough technique (27). All of these techniques will be performed when patients receive oxygen. These patients will then receive inspiratory hold technique with emphasis of diaphragmatic breathing.  Patients without airway secretions  These patients will receive inspiratory hold technique with emphasis of diaphragmatic breathing.  These techniques will be done in 3 sets with 10 repetitions:  **First set:** hold breath for 3 seconds, rest for 6 seconds  **Second set:** hold breath for 6 seconds, rest for 12 seconds  **Third set:** hold breath for 10 seconds, rest for 20 seconds  From the third session onwards, the patient will be asked to walk in the ward area (with/without using oxygen) after receiving treatment, walk for a maximum of 6 minutes. Factors which determine the end of the walk are:   - 1. O_2_ saturation reaches 80%   2. Rating of perceived exertion based on Borg scale: 11-13 (36)   In the end, instructions will be given to patient about effective cough (in case of any secretion), upper respiratory muscle relaxation and diaphragmatic breathing.  **Data collection method and tools:**  **Primary Outcome Measurements:**   - VBG analysis: Blood sample will be taken from a peripheral vein after 2-minute breathing in free room air. Factors such as PH, PvCO_2_, PvO_2_ and O_2_ saturation will be extracted from this analysis. As non-intubated patients with COVI-19 mostly don’t have arterial line, sampling from artery and performing arterial blood gas will be every painful and unethical. Apart from that, these patients have a respiratory (not cardiac) condition which based on previous studies there is a significant correlation between arterial and venous analysis (30). - 3-minute-walk test: Based on previous studies, this test is a simple cheap way with submaximal intensity that can be used in either in and out-patient setting. Also, there is a significant correlation between this and 6-minute-walk test (19, 20).   The patient will be asked to walk a smooth pathway with maximum speed possible for him/her in 3 minutes. Patient must have comfortable footwear during participating in this test. The patient will be instructed to stop walking and inform by the to stop walking if any sign of pain, inability, dyspnea and etc. occurred. During the test, the investigator won’t encourage the patient to increase his/her speed. After finishing the test, the patient is asked to stop and the investigator will measure the travelled distance.  If any cardio-vascular consequences or conscious disturbance occurs during operating this test, the physiotherapist will call for the physicians.   - Measuring O_2_ saturation after 2-minute breathing via partial rebreather: in this test, the patient will be asked to be in Fowler position for 2 minutes. A partial rebreather mask will be fixed on his/her face. Then the patient is asked to breathe deeply via the mask. After 2 minutes, the O_2_ saturation will be measured with a pulse oximeter.   **Secondary Outcome Measurements:**   - Level of breathlessness: At first, a visual analogue scale (VAS) image is given to the patient. The patient will be instructed that zero stands for no breath shortness and 10 shows maximum breath shortness. The patient will be asked to mark his/her feeling of breath shortness during past 24 hours on the paper with a pen. - Rating of perceived exertion based on Borg scale: On this scale 6 is very mild trouble and 19 is severe trouble during or after doing activities. The patient will be instructed to state his/ her dyspnea using this scale. - Health-related quality of life: One month after finishing the interventions, the patient will be contacted and will be asked to fill the short form-36 quality of life questionnaire. - Mortality rate: Based on the patient’s medical record, the patients’ related-mortality rate until one month will be evaluated   **Treatment protocol development:**  One of the main aims of this study is to develop a treatment protocol for managing (evaluation and treatment) hospitalized patients because of COVID-19 pneumonia on behalf of Tehran university of medical sciences. To achieve this goal, after finishing this RCT, a systematic review of all the published studies related to the physiotherapy program of these patients in the inpatient phase will be provided. Search and data extraction in this systematic review will be according to PRISMA standard. After data extraction, assessing the studies quality and this RCT report, the result will be presented in an expert panel including physiotherapists and other related medical fields experts to express their views. The main investigator will gather and classify all the views. Considering the level of their evidence and quality, a draft for the protocol text will be written. This text will be presented again in the expert panel for evaluating its content validity. Another version of the draft will be provided after applying the changes made by the expert panel and will be given to 5 physiotherapists visiting patients with COVID-19. They will be asked to express their views on the comprehension and unclear paragraphs (face validity). the output of these steps will provide physiotherapy protocol for hospitalized patients with COVID-19 induced pneumonia. Also, in order to ask the expert panel about their agreement to different parts of recommended protocol based on Delphi method. |

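### The 3-minute walk test, a primary outcome done at maximum speed by hypoxaemic patients, has a symptom-based stop only and no stated oximetry, saturation limit or oxygen condition

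*Protocol*

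**What the plan says.** The Protocol's Research Design and Methods lists three primary outcomes: venous blood gas analysis, the 3-minute walk test, and saturation after breathing through a partial rebreather.

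For the walk test, the pace instruction is "The patient will be asked to walk a smooth pathway with maximum speed possible for him/her in 3 minutes". The investigator gives no encouragement. The patient is "instructed to stop walking and inform by the to stop walking if any sign of pain, inability, dyspnea and etc. occurred". There is also an escalation rule: "If any cardio-vascular consequences or conscious disturbance occurs during operating this test, the physiotherapist will call for the physicians". The section on definitions adds that all patients do the test before and after the interventions, with allowance for their individual condition, but it does not say what that allowance is.

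Eligibility requires "O2 Saturation < 88% when free air breathing", with no lower bound. Patients must also be able to walk and exercise.

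The experimental arm has a second, separate walk: "From the third session onwards, the patient will be asked to walk in the ward area (with/without using oxygen) after receiving treatment". It lasts at most 6 minutes and ends on either of two factors: "O_2_ saturation reaches 80" percent, or "Rating of perceived exertion based on Borg scale: 11-13".

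The other two primary outcomes state what the patient breathes: room air for 2 minutes before the blood sample, and a partial rebreather mask for 2 minutes before the saturation reading.

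**The concern.** Two things are at stake.

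The first is safety. The patients are hypoxaemic by definition, and the test asks for the fastest walk each can manage, first at baseline. Its stop depends on symptoms. The only walk in the protocol with a saturation limit is the later, exertion-limited ward walk. An investigator could follow the walk test instructions exactly and let a patient with few symptoms continue below a value at which the same protocol ends another walk.

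The second is measurement. Walked distance in hypoxaemic patients can depend on whether they are breathing oxygen. If a patient uses oxygen at one time point and not at the other, the change in distance is partly an oxygen effect. The protocol compares this distance before and after and between groups, so the condition should be the same at both time points.

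**Working it through.** No figure in the protocol is to be reproduced here. The check is a comparison of texts and a little arithmetic on the stated thresholds.

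**Step 1. Order of events.** The Methods text runs: consent, evaluation with all outcome measurements including the walk test, envelope randomization, intervention. The definitions section adds a repeat after the interventions. So every patient does the test at baseline, and those still in the study do it again.

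**Step 2. The two walks side by side.**

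| | 3-minute walk test | Ward walk |
| --- | --- | --- |
| Who | Both arms | Experimental arm |
| When | Before randomization and after the intervention | From the third session |
| Duration | 3 minutes | At most 6 minutes |
| Pace | Maximum possible for the patient, no encouragement | Limited by exertion (Borg 11-13) |
| Stated stop | Symptoms | Saturation of 80%, or Borg 11-13 |
| Oximetry during the walk | Not stated | Implied by the saturation limit |
| Oxygen | Not stated | Left open (with or without) |

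**Step 3. The three primary outcomes side by side.** Blood gas: room air. Saturation: partial rebreather mask. Walk test: none stated. So 2 of 3 name the breathing condition and 1 does not.

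**Step 4. Headroom, if the test is done on room air.** Entry is below 88% and the ward walk ends at 80%. Since 88 - 80 = 8, resting room-air saturation is less than 8 points above that limit. A patient enrolled at or below 80% has no headroom. If the test is done on oxygen, this figure does not apply.

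**Step 5. Number of tests.** The sample size section plans 20 per group to allow for attrition from a required 13 per group.
- Baseline: 2 x 20 = 40.
- Follow-up: from 2 x 13 = 26 to 2 x 20 = 40.
- Total: 40 + 26 = 66 to 40 + 40 = 80.

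This counts exposure to the gap. It is not an effect size.

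**Step 6. What cannot be computed.** The document gives no distribution of saturation at entry or during walking, and no figure for the effect of oxygen on distance. Neither the share of patients who would fall below 80% nor the size of any distortion in distance can be derived.

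**The case against.** The strongest reply is that this is silence and not error. Nothing forbids oximetry, oxygen or an earlier stop. The test has real safeguards: ability to walk as an entry criterion, a symptom stop with an open-ended list, no encouragement, a physician call, and a general allowance for the patient's condition. Patients are in pre-intensive or intensive care units, and a ward procedure not shown here may cover monitoring. All of this is fair, and it limits the point to what could happen. It does not remove it: none of the stated safeguards is triggered by a saturation value, and the measurement procedure of a primary outcome belongs in the protocol, not in an analysis plan.

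The ward walk is also an imperfect comparator. Its 80% limit stands beside an exertion limit and may be there for dosing as much as for safety; the protocol does not say. It lasts up to twice as long, and it leaves oxygen open, so it is a precedent for a saturation stop but not for a fixed oxygen condition. Similarly, a blood gas or saturation reading needs the inspired gas to be interpretable at all, while a distance depends on it less directly. These points weaken the contrast but leave the gap.

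A reader might infer more than the text supports:

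- **That the two walks contradict each other.** They do not; both can be followed.
- **That one arm is less protected during the test.** The test is the same in both arms; the difference is between two procedures.
- **That the arm comparison is biased.** Oxygen switching that is equal in both arms only adds noise. Bias needs switching that differs by arm. That is conceivable if treatment changes oxygen need, but the document does not show it.
- **That calling the test submaximal ("this test is a simple cheap way with submaximal intensity") conflicts with the maximum-speed instruction.** A self-paced, unencouraged walk can be submaximal, so nothing rests on this.
- **That the broken wording of the symptom stop is itself a defect.** A word may have been lost in translation or in reading the file, so it carries no weight.

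**Conclusion.** The point stands in a limited form. As written, the walk test lets a patient with few symptoms continue below 80% saturation and lets oxygen use differ between the two time points. It is a cheap improvement in patient safety and measurement comparability, not proof of harm or bias. The exposure is 66 to 80 tests, on the assumption that 20 per group are enrolled and 13 to 20 per group return. The headroom of under 8 points holds only on room air. The size of any effect cannot be computed from the document. The textual absence is certain; the consequences are possible, and how often they would occur is unknown.

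**What to change.** Add to the walk test procedure:

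1. Monitor saturation throughout with the pulse oximeter already used for the saturation outcome.
2. End the test when saturation reaches 80%, the limit the protocol already uses, in addition to the symptom stop.
3. Record the distance reached, the lowest saturation and the reason for stopping.
4. Use the same oxygen condition (device and flow) for each patient at both time points, chosen by one rule in both arms. If a patient's clinical state requires a different flow at the second test, give it and record the departure.

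Do not carry over the ward walk's Borg 11-13 stop. Perceived exertion after the test is a secondary outcome, and that stop would cap it.

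The cost is a few lines of protocol text and two or three case report form fields. The downside is that some tests will end early with shorter distances, and a distance walked on oxygen describes capacity on oxygen. For a patient already at or below 80% under the chosen condition, the limit is met at the outset; whether to test such a patient, and how to record it, is a clinical decision to be settled in advance and identically in both arms.
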